### Stepped-wedge cluster randomized trial design

The intervention materials developed through the crowdsourcing open call will be delivered in a stepped-wedge cluster randomized trial. This stepped wedge design will be a four-phased implementation (four clusters) with each cluster starting the intervention at three-month intervals (Table 1).

### Cluster randomization

Block randomization will be used to control for potential secular trends and bias related to the imbalance in cluster-level covariates [30]. Block size will be eight. Participants at each site will be assigned to blocks based on the timing of PrEP initiation. Participants enrolled at the same site will be grouped to the same block. Blocks will be assigned to the four clusters using a computer-generated randomization list that is generated by a study staff member.

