**Methods:**

The study will develop intervention packages to facilitate PrEP adherence among Chinese key populations using co-creation methods. The study will then evaluate the efficacy of the co-created intervention packages using a stepped-wedge randomized controlled trial. This four-phased closed cohort stepped-wedge design will have four clusters. Each cluster will start intervention at three-month intervals. Seven hundred participants who initiated PrEP will be recruited. Participants will be randomized to the clusters using block randomization. The intervention condition includes receiving co-created interventions in addition to standard of care. The control condition is the standard of care that includes routine clinical assessment every 3 months. All participants will also receive an online follow-up survey every 3 months to record medication adherence and will be encouraged to use a WeChat mini-app for sexual and mental health education throughout the study. The primary outcomes are PrEP adherence and retention in PrEP care throughout the study period. We will examine a hypothesis that a co-created intervention can facilitate PrEP adherence. Generalized linear mixed models will be used for the primary outcome analysis.

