### Sample size

A total of 700 participants will be recruited from Hubei and Guangdong provinces. The sample size of this closed cohort, binary outcome, complete stepped-wedge RCT design was calculated using PASS Sample Size Software (NCSS LLC, Kaysville, Utah). The required sample size was calculated for the primary outcome. We assumed that a crowdsourced intervention will facilitate PrEP adherence among at-risk populations compared to the standard routine follow-up. This calculation was based on the Hussey and Hughes model postulating the cluster-specific departure from the average is homogeneous across time periods and intervention sequences [28, 29]. We assumed an intra-cluster correlation coefficient (ICC) of 0.02. Assuming an intervention effect of 0.2 (0.6 under intervention, 0.4 under control), a total of four clusters, four total intervention time periods. Two-sided Wald Z-Test alpha = 0.05, 80% power, the total sample size was 540. Accounting for 20% lost to follow-up, we increased the total sample size to 700 (175 for each cluster).

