### Analysis

The primary outcome will be evaluated at the end line. We will examine a hypothesis that a crowdsourced intervention can facilitate PrEP adherence. As this is a binary outcome with a small number of clusters, we will use generalized linear mixed models (GLMM) for the primary outcome analysis [31]. It is appropriate to assume that the intervention effect is common across clusters as the intervention will be implemented to all clusters directly by CBO staff. The model will include intervention status and time as fixed effects given the potentially increasing loss-to-follow-up. The estimated intervention effects will be reported with 95%CIs and *p* values.

All secondary outcomes will be binary (continuous variables will be categorized into binary variables). Similar analysis will be conducted for secondary outcomes including proportion of people who test for HIV in the past 3 months, proportion of mhealth use, proportion of people who feel confident in their self-efficacy, and HIV incidence. Descriptive data will be used to summarize clusters.

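### The four "clusters" are start-time sequences, so the four-cluster power calculation does not describe this closed cohort, and a model with those groups as its only random level would miscalibrate the primary test

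*Protocol article*

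**What the plan says.** All references are to the protocol article.

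- **Allocation.** Cluster randomization forms blocks within site by when PrEP was started: "Block size will be eight", "Participants enrolled at the same site will be grouped to the same block", and "Blocks will be assigned to the four clusters using a computer-generated randomization list". The abstract's Methods paragraph differs: "Participants will be randomized to the clusters using block randomization".
- **Power.** Sample size uses "the Hussey and Hughes model postulating the cluster-specific departure from the average is homogeneous across time periods and intervention sequences", with "a total of four clusters, four total intervention time periods". It gives one correlation, an ICC of 0.02, and proportions of 0.4 and 0.6. The result is 540 for 80% power at two-sided 0.05, raised to 700 (175 per group) for 20% loss.
- **Cohort.** Study design and rationale describes a closed cohort. Study measures and outcomes assesses everyone at 3, 6, 9 and 12 months.
- **Analysis.** The model is chosen thus: "As this is a binary outcome with a small number of clusters, we will use generalized linear mixed models (GLMM". Intervention status and time are listed as fixed effects. No random effect is named.
- **Exposure.** The section on receiving the intervention materials gives each group three months of intervention. The Control condition section puts groups in the control condition at all other times.

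**The concern.** A cluster in the Hussey and Hughes sense is a pre-existing unit whose members share an outcome level, and which is itself randomised to a start time. Here the groups are put together by the randomisation, so they are the start-time sequences. What correlation there is lies mainly between the four measurements on one person, with possibly a little within a block of eight neighbours in recruitment order. The stated power model has a term for neither.

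Two things are at stake. The stated sample size and 80% power may describe a different design. And if the primary model carries the same structure, its confidence interval and p value depend on a variance estimated from four groups, while the within-person correlation is left unmodelled.

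**Working it through.** **1. Unit allocated.** On the literal wording of Cluster randomization there are 700/8 = 87.5, about 88 blocks, or about 22 per group. On the abstract's wording there are 700 participants. On neither reading are there four randomised units.

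**2. Reproducing 540.** The Hussey and Hughes variance for I clusters and T periods is

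Var = I s (s + T t) / [(I U - W) s + (U^2 + I T U - T W - I V) t],

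where s is the residual variance of a cluster-period mean, t the cluster variance, U the number of exposed cells, W the sum of squared period totals and V the sum of squared cluster totals.

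Inputs: I = 4; T = 5 (a baseline plus the four stated intervention periods); exposure sustained once started, so U = 10, W = 30, V = 30. Total variance is 0.24 (0.4 x 0.6, the same in both conditions) and the ICC is 0.02, so t = 0.0048 and s = 0.2352/m with m observations per cluster-period.

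At m = 27: s = 0.008711; numerator 4 x 0.008711 x (0.008711 + 0.024) = 0.001140; denominator 10 x 0.008711 + 30 x 0.0048 = 0.2311. Var = 0.00493 and SE = 0.0702. Power = Phi(0.2/0.0702 - 1.96) = 81.3%. At m = 26 power is 79.97%, so 27 is the smallest m reaching 80%.

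4 x 5 x 27 = 540, exactly the stated figure. Other settings miss it: variance 0.25 gives 560; four periods give 464 or 480; three-month exposure gives 256 to 340. In a closed cohort the same 27 people fill all five periods of a group, so the formula taken at face value asks for 4 x 27 = 108 people. Dropout: 540/0.8 = 675, rounded up to 700.

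**3. Power for this design.** The within-person correlation r is not in the document; I take 0.3 to 0.7. With block ICC 0.02 and 700 people, the SE of the risk difference is about 0.016 to 0.024 under sustained exposure and 0.011 to 0.018 under three-month exposure. Even at 0.024, 0.2/0.024 = 8.3. Power exceeds 99% at 540 or at 700.

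**4. Calibration of the primary test.** Linear scale, four follow-ups, 0.8 x 175 = 140 per group, r = 0.5 assumed, no block effect. Type I error = 2[1 - Phi(1.96 x model SE / true SE)].

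| Model | Exposure | Model SE | True SE | Type I error |
|---|---|---|---|---|
| Group variance zero | sustained | 0.0262 | 0.0321 | 11% |
| Group ICC held at 0.02 | sustained | 0.0353 | 0.0246 | 0.5% |
| Group variance zero | three months | 0.0239 | 0.0169 | 0.6% |
| Participant intercept | sustained | 0.0239 | 0.0239 | 5% |
| Participant intercept | three months | 0.0169 | 0.0169 | 5% |

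First row: model SE = sqrt(4 x (0.24/140)/10) = 0.0262, and the true SE is larger by sqrt(1 + r) = 1.225. Third row: model SE = sqrt(4 x (0.24/140)/12) = 0.0239, and the true SE is smaller by sqrt(1 - r) = 0.707. For r from 0.3 to 0.7 the first row runs from 8.6% to 13.3%.

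**5. Participant against block.** With 700 people, a true block ICC of 0.02 and a participant intercept only, type I error is 5.1% to 5.9% under sustained exposure and 5.0% under three-month exposure. The participant term does nearly all the work.

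**The case against.** The strongest reply is that the article never states the random structure of the primary model. The Hussey and Hughes description belongs to the sample size; the Analysis section names only fixed effects, and random effects are commonly left to an analysis plan. If that plan has a participant intercept, the intervals are about right. This stands. A reader might infer that the primary intervals are wrong as planned; the document does not support that, and the calibration point is conditional.

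A reader might also take the block of eight as the established unit, with 88 blocks as the proper basis for power. The abstract's wording, and a block size that is a multiple of four, also fit ordinary permuted-block allocation of individuals. What the document supports is that the two statements conflict.

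The error rates in the table are conditional extremes. In a simulation that estimates the group variance by REML under sustained exposure, the variance came out at zero in about a third of trials and overall type I error was 4.7%, 3.9% and 2.3% for r = 0.3, 0.5 and 0.7. So the test is not necessarily anti-conservative on average. But one trial falls in one case or the other, and under three-month exposure the same simulation gave 2.5%, 0.5% and 0.03%.

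The groups also receive different intervention versions (1.0 to 4.0), so group is a delivery unit too. A group intercept constant over time does not capture a difference between versions, and the Analysis section assumes a common effect.

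Finally, that 175 is not a multiple of eight is of no consequence: it is a planning average, and a last block can be incomplete.

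**Conclusion.** The concern holds in a limited form. The four groups are sequences under either account of allocation, and the article fixes both the power calculation and the reason for the mixed model on treating them as clusters. The stated 540 and 80% do not describe a closed cohort with repeated measures. That 540 counts person-period observations is an inference from an exact numerical match; it relies on a baseline period, although adherence is listed only at 3, 6, 9 and 12 months, and on sustained exposure, although each group gets three months.

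A reader might infer that the trial is too small. It is not, for the stated 0.2 difference: power exceeds 99%.

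If the four groups are the only random level, the primary test is miscalibrated. The direction depends on exposure coding and on whether the group variance is estimated at zero: about 0.5% to 11% type I error at r = 0.5. These figures are linear approximations to a binary mixed model and rest on an assumed within-person correlation. With a participant intercept the problem largely disappears.

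**What to change.** 1. Reconcile the abstract with Cluster randomization and state whether blocks or participants are randomised.
2. Call the four groups sequences, and drop the few-clusters reason for the mixed model.
3. Specify the primary model with a participant random intercept, plus a block intercept if blocks are the randomised unit. Include fixed effects for site (blocks are formed within site), assessment time and exposure.
4. Restate sample size and power as a closed cohort, with a declared within-person correlation and a range around it, using the exposure pattern actually planned.

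The cost is wording, one recalculation, and keeping participant, block and site identifiers in the analysis file; the study already needs these for allocation and for linking surveys. No additional enrolment is needed.

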### Intervention condition - receiving the intervention materials

Participants will be assigned into four clusters in blocks at each site. All clusters will receive the intervention initiated at a different time. Updated interventions 2.0, 3.0, 4.0 will be implemented for clusters b, c, d, respectively, in addition to cluster a receiving intervention 1.0. Each cluster will receive the intervention for 3 months over a 12-month period. The first intervention will start 2 weeks after the baseline recruitment. The time intervals of the crowdsourced intervention are aligned with the follow-up intervals in the PrEP Demo study. That is, the first cluster will receive their first intervention 2 weeks after they fill out the baseline survey, and the second, third, and fourth cluster will receive their first intervention 2 weeks after they complete the follow-up surveys at 3, 6, 9 months respectively. The intervention will be delivered to each cluster biweekly in the 3-month intervention period by the CBOs. CBO peer educators or volunteers will contact participants via WeChat and implement the intervention each time.

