### Control condition

When clusters are not in the intervention condition, they will be in the control condition. Control condition includes a baseline program using WeChat mini-app to promote sexual and mental health awareness and routine follow-ups by CBOs and hospitals. This mini-app promoting sexual and mental health awareness among Chinese gender and sexual minorities is predesigned by the research team and will be directly accessed on WeChat mini-app store for free [25]. The mini-app comprises synthesized LGBTQ-friendly information on PrEP (what is PrEP, benefits of PrEP, who can use PrEP, how to use PrEP, etc.) and other sexual and mental health-related content, and allows participants to apply for free HIV self-tests and communicate with study staff members directly. Participants will be introduced to the mini-app at baseline recruitment and will be encouraged to use the mini-app throughout the study. Participants will also receive follow-ups from the hospitals and CBOs at 3-month intervals to assess PrEP uptake and adherence. The follow-ups include an online follow-up survey to track PrEP adherence and a clinical assessment for ongoing PrEP uptake. The follow-up survey will be administered by CBO peer educators or volunteers, who will be responsible for sending out the survey and collecting survey responses. The clinical assessment will be performed by experienced physicians in the hospitals following standard guidelines.

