### Timeline

The study will span approximately 15 months (Table 1). The first 3 months will be the preparation phase. A crowdsourcing open call will be promoted and held to generate an initial crowdsourced intervention 1.0. Interventions 2.0, 3.0, 4.0 will be developed during the trial with inputs from the ongoing open call. The following 12 months will be the intervention phase. The intervention will be sequentially rolled out in each of the four clusters following the stepped-wedge design. Participants will be surveyed at baseline and every 3 months thereafter. By the 15th month, all participants will have received the intervention for a 3-month interval and the final follow-up survey will be conducted. The SESH research group will manage and oversee intervention progression.

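### Each cluster is given one 3-month exposure and then returns to control, but the sample size assumes permanent crossover and the model has no post-intervention state, so half of the control cells are ambiguous

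*Protocol article*

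**What the plan says.** The section on receiving the intervention materials says: "Each cluster will receive the intervention for 3 months over a 12-month period". Cluster a starts after baseline; clusters b, c and d start after the 3-, 6- and 9-month surveys. The Timeline section agrees: "By the 15th month, all participants will have received the intervention for a 3-month interval and the final follow-up survey will be conducted". The Control condition section adds: "When clusters are not in the intervention condition, they will be in the control condition". It makes no exception for clusters that have already been treated.

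The Sample size section describes another layout: "The sample size of this closed cohort, binary outcome, complete stepped-wedge RCT design was calculated using PASS Sample Size Software". It uses the Hussey and Hughes model with four clusters, four intervention periods, ICC 0.02 and 0.6 versus 0.4, and arrives at 540 before loss to follow-up. The Study design and Stepped-wedge design sections also present a stepped wedge with starts three months apart.

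The Analysis section plans a generalized linear mixed model with intervention status and time as fixed effects. It also says "The primary outcome will be evaluated at the end line" and "It is appropriate to assume that the intervention effect is common across clusters", the latter because CBO staff deliver to all clusters. Yet "Updated interventions 2.0, 3.0, 4.0 will be implemented for clusters b, c, d, respectively", while cluster a receives 1.0.

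**The concern.** In a complete stepped wedge a cluster has two states, before and after crossover. The delivery described here creates three: not yet treated, in the 3-month intervention, and after it. A two-level status term must put the third state somewhere, and the article points both ways. The Control condition section suggests control; the sample-size design implies intervention.

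The materials are educational images meant to raise PrEP awareness and knowledge, so some lasting effect is plausible, and no washout is planned. The remark in the Study design section that the components start and finish at once concerns implementation lag, not duration of effect. What is at stake is the meaning and the size of the primary estimate.

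**Working it through.** **1. The plan's own figure.** Inputs from the Sample size section: rates 0.6 and 0.4 (variance 0.6 × 0.4 = 0.24), ICC 0.02, 4 clusters, two-sided alpha 0.05. With a baseline and four steps there are T = 5 periods. The Hussey-Hughes variance is

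Var = Iσ²(σ² + Tτ²) / [(IU − W)σ² + (U² + ITU − TW − IV)τ²].

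Under permanent crossover I = 4, U = 10, W = 30, V = 30. With 27 per cluster-period, σ² = 0.24 × 0.98/27 = 0.00871 and τ² = 0.24 × 0.02 = 0.0048.

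- Numerator: 4 × 0.00871 × (0.00871 + 0.024) = 0.00114.
- Denominator: 10 × 0.00871 + 30 × 0.0048 = 0.2311.
- SE = √(0.00114/0.2311) = 0.0702; power = Φ(0.20/0.0702 − 1.96) = 0.81.

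Twenty-seven is the smallest cell size reaching 80%, and 27 × 4 × 5 = 540. The stated figure is reproduced exactly. For a 3-month exposure followed by control, the required total falls to 256–340, depending on variants. The 540 therefore belongs to permanent crossover.

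**2. The layout as delivered** (N = not yet treated, I = in intervention, A = after):

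| Cluster | Month 3 | Month 6 | Month 9 | Month 12 |
|---|---|---|---|---|
| a | I | A | A | A |
| b | N | I | A | A |
| c | N | N | I | A |
| d | N | N | N | I |

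Of 16 cells, 4 are I and 12 are off intervention: 6 N and 6 A.

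**3. Status on only while in intervention.** Each cluster and each period has exactly one I cell, so cluster and period effects cancel. The estimate is the mean of the 4 I cells minus the mean of the other 12. If shares p1, p2, p3 of δ remain one, two and three periods later, these occur in 3, 2 and 1 cells:

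E[estimate] = δ × [1 − (3p1 + 2p2 + p3)/12].

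With constant p this is δ × (1 − p/2). Adding the untreated baseline does not change it.

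| Persistence (p1, p2, p3) | Ratio to δ | Estimate if δ = 0.20 |
|---|---|---|
| 0, 0, 0 | 1.00 | 0.200 |
| 0.25 throughout | 0.875 | 0.175 |
| 0.5 throughout | 0.75 | 0.150 |
| 1 throughout | 0.50 | 0.100 |
| 1, 0.5, 0 | 1 − 4/12 = 0.67 | 0.133 |
| 0.5, 0.25, 0.125 | 1 − 2.125/12 = 0.82 | 0.165 |

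**4. Status kept on after crossover.** Generalized least squares with period effects returns δ exactly if the effect persists fully and constantly. If it vanishes, the 4 × 4 layout without baseline gives about 0.62 × δ at a correlation of 0.02 between a cluster's period means and 1.17 × δ at 0.9. With a baseline period and ICC 0.02, a 0.20 effect is estimated as 0.170 (27 per cell) or 0.193 (175 per cell).

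**5. Candidate models.**

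- One pooled after-state recovers δ if persistence is constant. If it fades as 1, 0.5, 0, the in-intervention estimate is 1.07, 1.25 and 1.39 × δ at correlations 0.02, 0.5 and 0.9 without baseline, and 1.07, 1.19 and 1.24 with it. The reason is that no cluster is still untreated at month 12.
- Separate terms for the first, second and third period afterwards recover δ exactly in every case.
- Standard errors at 135 per cluster (540/4), within-person correlation 0.5 assumed, no baseline: two-level status on only while in intervention, √[(0.24/135) × 0.5 × (1/4 + 1/12)] = 0.0172; pooled after-state, 0.0243; separate terms, 0.0267.

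**The case against.** The strongest reply is that no bias has been shown. The Analysis section does not say how status is coded after the three months, the Control condition section describes what participants receive rather than a coding rule, Table 1 is not shown in the text available, and an analysis plan may settle the matter. That stands: the defect is an unresolved contradiction, not an established bias. It does not remove the point, because the article's own sections imply opposite codings and neither is safe without knowing how long the effect lasts.

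The 7- and 30-day recall windows in Table 2 also help. The first 30-day window after the intervention opens roughly 6 to 8 weeks after delivery ends. This limits overlap with direct exposure for self-report, but it does not exclude lasting behaviour change.

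Three stronger readings are tempting and not supported.

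- A reader might infer that the effect will be halved. That needs full, constant persistence together with coding of the after-periods as control.
- A reader might infer that the trial is underpowered. At 540 observations, power at full persistence would be 0.46. But 540 matches cluster-period observations; with 135 to 175 participants per cluster measured each period, it stays at about 0.99 even for the halved effect.
- A reader might infer that month 12 alone is analysed, when nobody is untreated. The outcomes section refers to the whole study period, Table 2 lists months 3, 6, 9 and 12, and the model has a time effect. The end-line phrase more plausibly gives the timing of the analysis.

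Updating the materials is disclosed as part of the intervention, so the version issue is mainly one of labelling.

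**Conclusion.** The concern holds in a limited form. The delivery and control sections describe a staggered 3-month exposure with return to control; the sample size describes permanent crossover; the single status term cannot represent both. Depending on coding and persistence, the primary estimate could run from half of the true effect to somewhat above it. It is unbiased under no persistence with one coding and under full, constant persistence with the other. The harm is to the interpretation and size of the estimate, not to power.

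These ratios assume an additive risk-difference scale and exchangeable correlation within clusters; a logistic mixed model would give similar but not identical values. All persistence values are assumptions, since the documents give none.

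Separately, version, cluster and treated period coincide. The estimate is therefore an average over versions 1.0 to 4.0, and shared delivery staff do not justify assuming a common effect of different content.

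**What to change.** Reconcile the Study design, Sample size and Stepped-wedge design sections with the sections on receiving the materials, the Control condition and the Timeline. Which delivery schedule applies is for the investigators to state.

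If the 3-month exposure stands, replace the two-level status in the primary model with an in-intervention term plus separate indicators for the first, second and third period after it, with not yet treated as reference. Use the 3-, 6-, 9- and 12-month assessments, and baseline where the outcome exists. The primary contrast is in intervention versus not yet treated. Report the later terms as persistence, noting that they rest on clusters a–c, a–b and a alone. Do not pool the after-periods in the primary model.

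Say that the end-line phrase refers to when the analysis is done. Describe the result as an average over versions and drop the staff-based justification.

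No change to recruitment, visits or data collection is needed. The cost is precision: an SE of about 0.027 instead of 0.017 under the assumptions above. The detectable difference at 80% power is then about (1.96 + 0.84) × 0.0267 = 0.075, well inside the planned 0.20.

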Each follow-up at the 3, 6, 9, 12 months will include an online survey and a clinical assessment. (Table 1) The online survey will collect data related to number of sexual partners, HIV testing, PrEP uptake (missing doses in the past 90, 30, 7 days for daily PrEP users vs. number of sex and number of doses taken in the past 90, 30 days for on-demand PrEP users), engaging in WeChat mini-app, and evaluation of crowdsourced PrEP adherence intervention. Participants will be assessed on their PrEP attitudes, PrEP stigma, PrEP use self-efficacy, HIV-related anxiety, social support and overall perceived stress using validated scales at 6 and 12 months. For all follow-ups, transgender participants will additionally respond to questions related to whether they are currently using gender affirming hormones, and if they were, whether they are concerned about drug-drug interaction and whether they have mentioned taking hormones to the doctors who are prescribing PrEP. The clinical assessment will include testing results related to HIV, STIs (syphilis, HBV, HCV), standard blood test, standard urine test, liver function test, and renal function test. If a participant seroconverts to HIV positive, their participation in the study will be terminated and they will be referred to their local provider or health department for antiretroviral therapy. Otherwise, participants will be prescribed TDF-FTC for another 3 months after each follow-up at 3, 6, 9 months.

The primary outcomes of this sub-study are PrEP adherence and retention in PrEP care throughout the study period. PrEP adherence will be measured by self-report in quarterly behavioral assessment surveys and pill count at clinical follow-ups among a subset (a total of 120 participants who initiate PrEP during the study in Guangdong will be sampled to receive pill count using systematic random sampling). Retention in PrEP care will be measured via self-initiated or physician-advised PrEP discontinuation, PrEP re-initiation, and self-initiated switch rates from once daily and on-demand regimens. Details about the study measures are illustrated in Table 2. Optimal daily PrEP adherence will be considered to be 6–7 pills weekly. Optimal adherence to an on-demand regimen will be defined as having two pills at least 2 h before each sexual encounter, followed by one pill 24 hours after the first dose and one pill after the second dose.

**Table 2 Tab2:** Outcome measures and timepoints of data collection

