**Primary outcomes**		
**Retention in PrEP care**	Number of participants completed clinical follow-ups	3, 6, 9, 12 months
**PrEP adherence**	1. Self-report in follow-up surveys: During the past 7 days and 30 days: (1) self-report taking once daily regimen: number of missed pills; perceptions of whether they had taken < 60%, 60–90%, or > 90% doses. (2) self-report taking on-demand regimen: number of sex events that are not covered by any PrEP (0 pills taken); correctly covered by PrEP (2 pills on the sex day (X) and X + 1, X + 2; or at least one pill taken on days X, X + 1, and X + 2 if the days between two sex events are less than one week); partially covered by PrEP (any other use). 2. Pill count at clinical visits: number of unused pills counted at each clinical follow-up (in-person or via phone) 3. Medical possession ratio: [(total days between first fill and end of follow-up) – (number of days without TDF-FTC in possession)] / total days of follow-up, based on medical refilling records	3, 6, 9, 12 months
**PrEP discontinuation**	120 days without TDF-FTC in possession based on medical refilling records.	3, 6, 9, 12 months
**PrEP reinitiation**	Number of participants who discontinued TDF-FTC according to the study definition and then successfully restart PrEP, based on self-report and medical refilling records.	3, 6, 9, 12 months

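### In clusters b, c and d the start of the intervention is tied to completing a follow-up survey, so the text gives non-completers no start, contrary to the Timeline's universal delivery

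*Protocol article*

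**What the plan says.** All references are to the protocol article.

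- **Start rule** (Intervention condition - receiving the intervention materials). For cluster a, "the first cluster will receive their first intervention 2 weeks after they fill out the baseline survey". For the others, "the second, third, and fourth cluster will receive their first intervention 2 weeks after they complete the follow-up surveys at 3, 6, 9 months respectively". No start is given for a participant who does not complete the survey in question.
- **Universal delivery** (Timeline). By month 15, "all participants will have received the intervention for a 3-month interval and the final follow-up survey will be conducted".
- **Follow-up and outcomes** (Study measures and outcomes; Table 2). "The primary outcomes of this sub-study are PrEP adherence and retention in PrEP care throughout the study period". "Each follow-up at the 3, 6, 9, 12 months will include an online survey and a clinical assessment". Table 2 measures retention as "Number of participants completed clinical follow-ups". For the other primary outcome, "PrEP adherence will be measured by self-report in quarterly behavioral assessment surveys and pill count at clinical follow-ups among a subset".
- **Model** (Analysis). "The model will include intervention status and time as fixed effects given the potentially increasing loss-to-follow-up". The section does not say whether status means assigned or received.
- **Condition** (Control condition). Condition is described for clusters, not for individuals: a cluster that is not in the intervention condition is in the control condition.

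**The concern.** In three of the four clusters, exposure begins only once something has happened after randomisation: the participant has completed a follow-up survey. That survey is half of the quarterly follow-up. The other half is the clinical assessment, whose completion is the Table 2 retention measure. The survey is also the main source of the adherence data. Cluster a has no such condition beyond entry to the study. Because the plan itself anticipates growing loss to follow-up, the condition would bind harder from b to c to d.

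Two things are at stake. First, people who stop responding before their cluster's turn would not be sent the intervention, so delivery differs by cluster for a reason related to outcome. Second, if the analysis coded status by actual start, intervention periods would hold only people known to be engaged at the previous survey, while control periods would also hold people already lost. A fixed effect for time does not correct this, because the selection occurs within each period.

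**Working it through.** **Figures used.** The start rule carries no figure of its own, so there is none to reproduce. From the Sample size section I take 20% loss to follow-up and 175 participants in each of four clusters (700).

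**Assumptions of mine.** The 20% accrues over 12 months at a constant quarterly rate; loss is permanent; survey completion follows loss. Steps 2 and 3 also assume that survey completion tracks clinic attendance and that the true effect is zero.

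**Step 1: who never starts.** Quarterly retention is q = (1 − 0.20)^(1/4) = 0.9457. The share reaching the gating survey at month 0, 3, 6 or 9 is q^0, q^1, q^2, q^3.

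| Cluster | Gating survey | Share reaching it | Never start, of 175 |
|---|---|---|---|
| a | baseline | 100% | 0 |
| b | month 3 | 94.6% | 9.5 |
| c | month 6 | 89.4% | 18.5 |
| d | month 9 | 84.6% | 27.0 |

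The total is 54.9, about 55 of 700 (7.8%). With 10% loss the total is about 27, and with 30% about 85.

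**Step 2: status coded by receipt, no true effect.** In each quarter one cluster is due for its three months of intervention. Measured in cluster units, the received group is n1 = q^(k−1) and its retention at the next visit is q. The not-received group is n0 = 4 − n1: the three other clusters, with retention q^k, plus the due cluster's non-starters, with retention 0. Its retention is therefore 3q^k / n0.

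| Month | n1 | n0 | Received | Not received | Gap | Weight n1·n0/4 |
|---|---|---|---|---|---|---|
| 3 | 1.0000 | 3.0000 | 94.6% | 94.6% | 0 | 0.7500 |
| 6 | 0.9457 | 3.0543 | 94.6% | 87.9% | 0.0672 | 0.7221 |
| 9 | 0.8944 | 3.1056 | 94.6% | 81.7% | 0.1286 | 0.6944 |
| 12 | 0.8459 | 3.1541 | 94.6% | 76.1% | 0.1848 | 0.6670 |

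A linear regression of visit completion on status plus period indicators gives the weighted mean gap: (0.0672×0.7221 + 0.1286×0.6944 + 0.1848×0.6670) / 2.8336 = 0.2611 / 2.8336 = 0.092. So a null intervention shows +9.2 percentage points. The same calculation gives +4.8 at 10% loss and +13.2 at 30%. This is on the risk-difference scale; the planned mixed model may report another scale.

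**Step 3: status coded by assigned schedule.** At every visit all four clusters have retention q^k, so every gap, and the pooled estimate, is 0.

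**Step 4: dilution under assigned status.** The average share reached is (1 + 0.9457 + 0.8944 + 0.8459)/4 = 0.92. An effect on an outcome still observed in non-starters, such as the refill-based possession ratio in Table 2, shrinks by about that factor if they receive nothing: 0.20 would become about 0.184. Participants who are lost for good return no later survey, so they do not dilute self-reported adherence.

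**The case against.** The strongest reply is that the sentence describes timing and is not a gate. It is offered as an explanation of how the intervention intervals line up with the demonstration study's follow-ups. Other sentences have every cluster starting at three-month intervals and receiving three months, and the Timeline has all participants receiving the intervention. Nothing says that non-completers are excluded. This has force: a reader might infer that the plan deliberately restricts exposure to survey completers, and the documents do not support that. But the rule is worded for the individual participant, offers no other start, and is what the peer educators and volunteers, who also send and collect the surveys, would follow. The conflict with the Timeline therefore stands.

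A second reply is that the 9-point false effect needs an analysis the article does not describe. That is right. A reader might infer from the term for intervention status that receipt is meant, and so that the retention result will be biased. The Control condition section defines condition by cluster, which points to assigned status and zero bias. The precise coding may also sit in an analysis plan that is not shown.

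Third, the trigger is an online survey while retention counts clinic visits, and re-initiation is itself a listed outcome, so permanent loss and perfect tracking overstate the link. This also stands, and it limits the size.

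Finally, a reader might infer that the intervention misses everyone who begins to disengage, or that adherence, the hypothesis in the Analysis section, is materially biased. Someone who skips pills but still answers the survey is reached. Any figure for adherence bias would need response and frailty values that the article does not give.

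**Conclusion.** The concern holds as a defect in the stated start rule. Taken literally, the rule leaves survey non-completers in clusters b, c and d without a start, delays late completers, makes delivery unequal across clusters, and cannot be squared with the Timeline's statement that all participants receive the intervention.

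On the plan's own 20% loss, about 55 of 700 would never start (range 27 to 85), given permanent loss at a constant rate that survey completion mirrors. The false retention effect of about 9 points (5 to 13) is conditional: it arises only under receipt coding and close tracking of clinic attendance by survey completion. Under the assigned cluster schedule it is zero, and the cost is unreached participants plus some dilution of retention or refill-based outcomes. The article does not establish that the primary analysis will be biased.

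This should be fixed, with moderate confidence; it does not invalidate the design.

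**What to change.** 1. In the section on receiving the intervention materials, anchor the start for clusters b, c and d to the scheduled date: 3, 6 and 9 months plus 2 weeks after the baseline survey, whether or not the follow-up survey has been completed, except for participants whose participation has ended.
2. Reconcile that section with the Timeline, so that both describe the same delivery.
3. In the Analysis section, state that intervention status follows the assigned cluster schedule.

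The cost is about two sentences. Delivery is by WeChat, so sending to non-responders is nearly free; the downside is that a few messages go to people who will not open them. The change to delivery has to be made before the clusters' start dates pass, because an analysis rule cannot restore exposure that was never delivered.
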